**Day 23 (Visit 5)**

- Vital Signs (body temperature, respiratory rate, blood pressure, and pulse)
- Adverse event query
- Battery of tests (Post-sleep questionnaire, VAS, and DSST, in this order; one hour [ $\pm$  15 minutes] after awakening)
- Drug dispensing for out-patient use
- Dispense outpatient PSQ and instruct patient to complete prior to the next scheduled visit

**Night 29  $\pm$  2 days (Visit 6)**

- Collect unused study drug and assess compliance
- Collect outpatient PSQ
- Urine pregnancy test for WOCBP, except those who have been postmenopausal for at least 1 year or are surgically sterile (result must be negative prior to dosing)
- Breathalyzer
- Pre-sleep questionnaire
- Review of concomitant medication
- Adverse event query
- Study medication administration (30  $\pm$  5 minutes prior to light off)
- PSG

**Day 30 (Visit 6)**

- Laboratory evaluations (hematology, biochemistry and urinalysis)
- Full standard 12-lead ECG
- Vital Signs (body temperature, respiratory rate, blood pressure, and pulse)
- Adverse event query
- BWSQ (prior to battery of test)
- Battery of tests (Post-sleep questionnaire, VAS, and DSST, in this order; one hour [ $\pm$  15 minutes] after awakening)
- Drug dispensing for out-patient use
- Dispense outpatient PSQ and instruct patient to complete prior to the next scheduled visit

**Every outpatient night during double-blind period**

- Take study medication 30 minutes prior to planned bedtime

### **10.2.2. Placebo wash-out period**

#### **Visit 7**

##### **Night 36 $\pm$ 2 days**

- Collect unused study drug and assess compliance
- Collect outpatient PSQ
- Urine pregnancy test for WOCBP, except those who have been postmenopausal for at least 1 year or are surgically sterile (result must be negative prior to dosing)
- Breathalyzer
- Pre-sleep questionnaire
- Review of concomitant medication
- Adverse event query
- Administration of single-blind treatment (30  $\pm$  5 minutes prior to light off)
- PSG

##### **Day 37 and End-of-study Evaluations**

End-of-study procedures will be performed the morning of Day 37

- Full physical examination
- Full standard 12-lead ECG
- Vital signs (body temperature, respiratory rate, blood pressure, pulse, and weight)
- Laboratory evaluations (hematology, biochemistry and urinalysis)
- Serum pregnancy test for women of childbearing potential (WOCBP), except those who have been postmenopausal for at least 1 year or are surgically sterile
- BWSQ (prior to the battery of tests)
- Battery of tests (Post-sleep questionnaire, VAS, and DSST, in this order; one hour [ $\pm$  15 minutes] after awakening))
- Adverse events query
- Review of concomitant therapy
- IVRS call to report patient completion

### **10.2.3. Early Termination Evaluations**

Efforts should be made so that early termination procedures happen as soon as possible after discontinuation.

- Full physical examination
- Full standard 12-lead ECG
- Vital signs (body temperature, respiratory rate, blood pressure, pulse, and weight)
- Laboratory evaluations (hematology, biochemistry and urinalysis)
- Serum pregnancy test for women of childbearing potential (WOCBP), except those who have been postmenopausal for at least 1 year or are surgically sterile
- Adverse events query
- Review of concomitant therapy
- IVRS call to report patient discontinuation

### **10.3. Study Restrictions**

- Patients may not consume any alcohol-containing beverages for 24 hours prior to reporting to a study visit where an overnight PSG will be performed. Patients will be checked with breathalyzers during all check-in procedures. If patients test positive for alcohol, the patients will not be able to continue in the study.
- Consumption of xanthine containing beverages or food and beverages (e.g., coffee, tea, soda, and chocolate) is not permitted after 1:30 PM while participating in this study. If a deviation occurs the day of an overnight PSG assessment, it must be noted in the source documents and on the electronic CRF.
- Patients are to refrain from strenuous exercise and contact sports (e.g., weight training, aerobics, and football) for 24 hours before a study visit where blood will be drawn and for 4 hours prior to reporting to a study visit where an overnight PSG will be performed.
- Patients are not permitted to smoke more than 10 cigarettes/day or use tobacco products during nightly awakenings.
- Patients should not travel more than 2 time zones during the study.

## **11. ASSESSMENT OF EFFICACY**

### **11.1. Objective Assessments**

- PSG
- DSST

#### **Polysomnography (PSG)**

Polysomnography is an overnight recording of sleep pattern and behaviors associated with sleep. A variety of sensors are applied with paste or tape to the body's surface to record brain waves, eye movements, muscle tone, body movements, heart rate, and breathing. The recording of the sensors can be helpful in determining sleep latency (the time that transpires between lights off and the onset of sleep), total sleep time, the time spent in each sleep stage, number of awakenings, WASO, and sleep efficiency (the ratio of total sleep time to time spent in bed, multiplied by 100). Normal sleep is separated into non-rapid eye movement (NREM) and rapid eye movement (REM) sleep. NREM sleep is further divided into 4 stages advancing from alert to asleep, with the lightest sleep occurring in Stage I sleep, and the deepest sleep occurring in Stage IV NREM sleep. NREM and REM sleep follow continuous cycles at approximately 90-minute intervals throughout the night. In addition, a diagnostic PSG includes channels to monitor air flow and limb movement to generate an AHI score and PLMAI score for evidence of sleep apnea and restless leg syndrome, respectively. A diagnostic PSG will be done on all patients on the first night of the placebo lead-in period. The diagnostic PSG will initially be scored locally by the site to determine if the patient still qualifies. The dPSG will be re-scored by the central facility. The rest of the PSGs will be done according to the schedule of evaluations (see [Table 2](#)) and scored by a central facility.

#### **Digit Symbol Substitution Test (DSST)**

The DSST is a subtest from the Wechsler Adult Intelligence Scale (Wechsler, 1955) that requires speedy recording of digits and symbols. It is used to measure psychomotor performance. It presents a code of 9 matched digits and symbols at the top of the test sheet. Patients are required to substitute a symbol for a digit from a code visible throughout the test. The number of correct items completed in 90 seconds is the score. Patients will be instructed on how to complete the DSST and take a practice test the first night of the placebo lead-in period. Additional DSST will be performed according to the schedule of evaluations (see [Table 2](#)) DSST will be administered approximately 1-hour after being awakened. The DSST will always be administered immediately after the VAS.

### **11.2. Subjective Assessments**

- Pre- and post-sleep questionnaires

- VAS
- BWSQ

### **Pre- and post-sleep questionnaires**

The pre- and post sleep questionnaires will be used in this study to assist assessing subjective sleep quality, depth of sleep, sleep latency, total sleep time, daytime function and daytime alertness. The pre-sleep questionnaire will be completed by the patient prior to study medication administration in the sleep clinic. The post-sleep questionnaire will be completed by the patient on both an inpatient and outpatient basis. In the sleep clinic, the PSQ will be completed approximately 1-hour after awakening immediately before the patients complete the VAS and DSST. A PSQ will also be given to each patient at the end of Visits 1 through 6 to take and complete at home. Patients should be instructed to complete the outpatient PSQ the morning of the next scheduled visit. These questionnaires will be completed by the patients as indicated on the schedule of evaluations (see [Table 2](#)).

### **Visual Analog Mood Scale (VAS)**

The visual analog mood scale is a self-rated scale designed to assess feelings, affect, and mood, and their changes. The visual analog mood scale is a nonverbal measure of internal mood states (e.g., afraid, confused, sad, angry, energetic, tired, happy or tense). The scales have a neutral word at one end of a 100 mm line and a “mood” adjective at the other. The respondents indicate the point on the line that best describes how they are currently feeling. Patients will be instructed on how to complete the visual analog mood scale and will be given a practice test at Visit 2. Additional VAS will be performed according to the schedule of evaluations (see [Table 2](#)). VAS will be administered approximately 1-hour after being awakened immediately after the PSQ.

### **Benzodiazepine Withdrawal Symptom Questionnaire (BWSQ)**

The Tyrer Benzodiazepine Withdrawal Symptom Questionnaire is a self-reported questionnaire which records the main symptoms experienced during withdrawal from benzodiazepines in pharmacologically dependent patients. The questionnaire consists of 20 symptoms. Each symptom is rated from 0 to 2. The absence of a symptom is rated as 0. The presence of a symptom is rated as either 1 or 2, with 1 being moderate and 2 being severe. The maximum possible score is 40. There are two versions of the BWSQ. The first version (BWSQ-1) is a retrospective assessment of the most severe symptoms experienced at any time during the use of, or the withdrawal from benzodiazepines. The second version (BWSQ-2) assesses symptoms within the immediate past (2 weeks) and it is appropriate for evaluating the frequency of symptoms during withdrawal. This study will use BWSQ-2 which will be completed at Day 30 ( $\pm 2$  days) and Day 37 ( $\pm 2$  days) as part of the EOS assessments. The BWSQ will be given to patients before the battery of tests (approximately 1 hour after awakening).

## 12. ASSESSMENT OF SAFETY

### 12.1. Safety Parameters

Safety assessments should be conducted as specified in the Schedule of Evaluations (see [Table 2](#)). These assessments include: the regular monitoring and recording of all AEs and SAEs; the regular monitoring of hematology, blood chemistry and urinalysis values; the regular monitoring of vital signs; and the performance of physical examinations and electrocardiograms. Any amendments to this protocol that change the schedule of visits and procedures will be included in the clinical study report for this protocol.

#### 12.1.1. Laboratory Evaluations

The Schedule of Evaluations (see [Table 2](#)) shows the time points at which blood will be collected for clinical laboratory tests and urine will be collected for urinalysis in the VP-VEC-162-3104 study.

[Table 3](#) presents the clinical laboratory tests to be performed.

**Table 3: Clinical Laboratory Tests**

| Category                                                                                         | Parameters                                                                                                                                                                                         |
|--------------------------------------------------------------------------------------------------|----------------------------------------------------------------------------------------------------------------------------------------------------------------------------------------------------|
| Hematology                                                                                       | Red blood cell count (RBC), hemoglobin, hematocrit, platelets, and white blood cell (WBC) count with differential (absolute counts of neutrophils, lymphocytes, monocytes, eosinophils, basophils) |
| Chemistry                                                                                        |                                                                                                                                                                                                    |
| Electrolytes                                                                                     | sodium, potassium, chloride, magnesium                                                                                                                                                             |
| Liver function test                                                                              | alkaline phosphatase, aspartate aminotransferase (AST [SGOT]), alanine aminotransferase (ALT [SGPT]), total bilirubin, gammaglutamyl transferase (GGT)                                             |
| Renal function parameters                                                                        | blood urea/blood urea nitrogen (BUN), creatinine                                                                                                                                                   |
| Other                                                                                            | glucose, calcium, albumin, total cholesterol, phosphorus, lactate dehydrogenase (LDH), total protein, uric acid, creatine kinase, amylase                                                          |
| Urinalysis                                                                                       |                                                                                                                                                                                                    |
| Gross and chemical exam                                                                          | color, appearance, specific gravity, pH, protein, glucose, ketone, blood, nitrite                                                                                                                  |
| Reflexive microscopic exam
(will be done if any of the
urinalysis testing is not negative) | RBC, WBC, epithelial cells, bacteria, casts, crystals                                                                                                                                              |

The clinical laboratory tests (hematology, chemistry, and urinalysis) will be performed by a certified central laboratory that will forward laboratory data to both the site and Vanda or its designee. Details regarding the collection, shipment of samples, reporting of results, and alerting of extreme values will be outlined in the Laboratory Manual, which will be supplied to all sites.

Values considered to be potentially clinically notable are provided in [Appendix 21.1](#) for the Investigator's guidance. Any laboratory test result that the Investigator considers clinically significant will be repeated once to rule out laboratory error. For tests where a

persistent abnormality is considered to be drug related, repeat analyses will be performed until the cause is determined and either a return to normality occurs or the Investigator deems the abnormality to be of no clinical significance. Any laboratory test result that the investigator considers clinically significant must also be recorded as an adverse event.

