### **14.10. Safety Data**

The primary assessment of safety will be based on the frequency of treatment-emergent adverse events and on the frequency of clinically notable abnormal vital signs and laboratory values.

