#### **14.10.2. Laboratory Data**

Laboratory data will be summarized for each treatment group by presenting the proportions of patients with clinically notable abnormalities ([Appendix 21.1](#)) as defined below; shift tables, baseline to most extreme post-baseline value, using normal ranges (extended normal ranges for laboratory data;  $\pm 10\%$  of normal range for electrolytes [sodium, potassium, and calcium] and  $\pm 15\%$  of the normal range for all other measures); summary statistics of raw data and change from baseline values (means, medians, standard deviations, ranges).

Clinically notable values will be identified according to the criteria identified in the FDA's "Supplementary Suggestions for Preparing an Integrated Summary of Safety Information in an Original NDA Submission and for Organizing Information in Periodic Safety Updates" (Revised 2-APR-87) provided by the FDA Division of Neuropharmacological Drug Products (DNPD).

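### In Appendix 21.1 the two columns of the BUN row contradict each other by a factor of 1000: 30 mg/dL is 10.7 mmol/L, but the SI column prints 10.7 μM.

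*Protocol*

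**What the plan says.** Protocol section 12.1.1, Table 3, lists the renal tests as "blood urea/blood urea nitrogen (BUN), creatinine" and names no reporting unit. The text below the table directs the investigator to the appendix: "Values considered to be potentially clinically notable are provided in" Appendix 21.1. In that appendix the BUN row gives a notable limit of 30 mg/dL or more under standard units and 10.7 μM or more under SI units. The protocol does not say which column governs.

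The table is put to use in three places:

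- Section 14.10 rests the primary safety assessment in part on the "frequency of clinically notable abnormal vital signs and laboratory values".
- Section 14.10.2 states: "Laboratory data will be summarized for each treatment group by presenting the proportions of patients with clinically notable abnormalities", with a reference to Appendix 21.1.
- Section 7.3 points to the same appendix as a guide when the investigator considers whether a patient should continue.

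**The concern.** A table with two unit columns should state one limit twice. In the BUN row the SI figure is far too small to be the equivalent of the mg/dL figure. The creatinine row alone suggests this. BUN at its limit has 15 times the mass concentration of creatinine at its limit (30 against 2.0 mg/dL), yet the SI column gives BUN about 16.5 times fewer moles (176.8 / 10.7). That would require urea nitrogen to be a far heavier species than creatinine, which it is not.

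What is at stake is one notable-value proportion in the safety tables and one line of investigator guidance. A limit set 1000 times too low is exceeded by practically everyone, so a proportion built on it cannot separate the arms.

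**Working it through.** **Inputs from Appendix 21.1 (standard units / SI units).** BUN 30 mg/dL / 10.7 μM; creatinine 2.0 mg/dL / 176.8 μM; uric acid, male, 10.5 mg/dL / 624.6 μM; uric acid, female, 8.5 mg/dL / 505.6 μM; total bilirubin 2.0 mg/dL / 34.2 μM.

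**Inputs not in the protocol.** Molar masses, taken as standard constants: urea nitrogen 28.013 g/mol (two nitrogen atoms per molecule of urea), creatinine 113.12, uric acid 168.11, bilirubin 584.66.

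**Formula.** μmol/L = (mg/dL × 10 / molar mass) × 1000.

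**Step 1: do the other molar rows reproduce?**

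| Row | Calculation | Result (μM) | Printed (μM) |
|---|---|---|---|
| Creatinine | 20 / 113.12 × 1000 | 176.8 | 176.8 |
| Uric acid, male | 105 / 168.11 × 1000 | 624.6 | 624.6 |
| Uric acid, female | 85 / 168.11 × 1000 | 505.6 | 505.6 |
| Bilirubin | 20 / 584.66 × 1000 | 34.2 | 34.2 |

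All four agree to the printed decimal, so the column follows the ordinary convention.

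**Step 2: the BUN row.** 300 / 28.013 × 1000 = 10,709 μM = 10.7 mmol/L. The printed figure is 10.7 μM, and 10,709 / 10.7 = 1,001, which is a factor of 1000 apart from rounding. The digits are right for mmol/L and wrong for μM.

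**Step 3: read the printed SI limit backwards.** 10.7 μmol/L × 28.013 μg/μmol = 299.7 μg/L = 0.030 mg/dL, against 30 mg/dL in the adjacent cell.

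**Step 4: could another reading of BUN rescue the row?** Counted per nitrogen atom (14.007 g/mol), 30 mg/dL is 21.4 mmol/L. Read as mass of whole urea (60.056 g/mol), it is 5.0 mmol/L. Both are thousands of μM, so neither comes near 10.7 μM.

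**Step 5: a check that assumes no molar mass.** The printed BUN pair implies 300 mg/L ÷ 10.7 μmol/L = 28.04 mg/μmol, or about 28,000 g/mol. The printed creatinine pair implies 20 mg/L ÷ 176.8 μmol/L = 0.1131 mg/μmol, or 113 g/mol. The first is 1000 times the mass of urea nitrogen; the second is correct.

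**Step 6: consequence if the SI column is applied.** The protocol gives no distribution of BUN, so take a deliberately low value for illustration: one tenth of the conventional limit, 3 mg/dL. That is 30 / 28.013 × 1000 = 1,071 μM, about 100 times the printed SI limit. Any realistic sample is flagged, at baseline and afterwards, on drug and on placebo.

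**The case against.** **Arguments that the row does no harm.** The conventional limit stands beside the SI figure. Section 9.2 has labels following US requirements, which suggests US sites, and section 12.1.1 has a single central laboratory reporting all results, so mg/dL may well be the working unit. Sections 14.10.2 and 21.1 name an FDA guideline as the source of the criteria, so the printed SI column is not the only reference. A flag that fires on every sample would also be noticed in routine data checks. All of this lowers the chance that the error reaches a table. It does not remove the contradiction, because the protocol prints both columns and does not choose between them.

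**Possible reading error.** The text was extracted from PDF and the platelet row of the same appendix is visibly broken, so a printed mM misread as μM cannot be fully excluded. The BUN cell itself is intact and, in the text available, reads μM.

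**Stronger readings that the protocol does not support.**

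- A reader might infer that a drug–placebo difference in BUN would vanish altogether. It would not. Section 14.10.2 also plans shift tables against extended normal ranges and summary statistics of raw values and changes from baseline, and none of these uses the Appendix 21.1 limit. Nor does the protocol define a composite of any notable chemistry value that this row could swamp.
- A reader might take the limits as binding rules for discontinuation. Sections 7.3 and 12.1.1 offer them as guidance and leave the judgement with the investigator.
- A reader might add that neutrophils and eosinophils are collected as "absolute counts of neutrophils, lymphocytes, monocytes, eosinophils, basophils" but judged in percent. Table 3 collects the total white cell count in the same panel, so percent = 100 × count / WBC is available. Where that derivation is written down is a matter for the analysis plan or the laboratory manual, not an error here.
- Listing blood urea next to BUN in Table 3 is likewise no error. Table 3 states no limit; the fault lies wholly in the appendix row.

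**Conclusion.** The point holds for one row. The standard and SI limits for BUN in Appendix 21.1 differ by a factor of 1000, and every other molar row in that table converts correctly. The finding rests on standard molar masses and on the text reading μM as extracted.

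The effect depends on the unit system. With SI units applied as printed, essentially 100% of samples are notable for BUN in every arm and that proportion is uninformative; investigators using that column would also have a guide value that every patient exceeds. With mg/dL there is no effect. Efficacy, sample size, type I error and the other safety displays are untouched in either case. It is a small but certain inconsistency in a table that the safety analysis calls by reference.

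**What to change.** Reconcile the two BUN entries in Appendix 21.1 before the laboratory flags are programmed. The printed number 10.7 matches 30 mg/dL only if the SI unit is mmol/L; the sponsor should confirm this against the source of the criteria. This aligns two statements of the same limit and proposes no new one. The cost is one unit in one table cell, plus a check that the flag specification and any investigator copy of the table carry the same entry. No change to data collection is needed.

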#### **12.1.2. Additional Laboratory Evaluations**

Blood and urine samples will also be collected for the following evaluations: serum pregnancy, urine drug screen for drug abuse, and urine pregnancy test (over-the-counter pregnancy test). These assessments will be performed according to the Schedule of Evaluations (see [Table 2](#)).

